### Data management {19}

The study participants’ contact information will be securely stored at each clinical site for internal use during the study. At the end of the study, all records will continue to be kept in a secure location for as long a period as dictated by the reviewing IRB, Institutional policies, or sponsor/funding agency requirements.

Study participant research data, which is for purposes of statistical analysis and scientific reporting, will be transmitted to and stored at KPWA and KPNW. This will not include the participant’s contact or identifying information. Rather, individual participants and their research data will be identified by a unique study identification number. The study data entry and study management systems will be secured and password protected. At the end of the study, all study databases will be de-identified and archived.

### Confidentiality {27}

Data that could be used to identify a specific study participant will be held in strict confidence within the research team. No personally identifiable information from the study will be released to any unauthorized third party without prior written approval of the sponsor/funding agency. All research activities will be conducted in as private a setting as possible.

### Plans for collection, laboratory evaluation, and storage of biological specimens for genetic or molecular analysis in this trial/future use {33}

This trial does not involve collecting biological specimens for storage.

## Statistical methods

### Statistical methods for primary and secondary outcomes {20a}

#### Analysis of the primary endpoint(s)

The trial has two primary outcomes, financial distress, and cancer-specific health-related quality of life (HR-QOL). Both of these outcomes are continuous measures, which will be assessed via survey at 12 months after randomization. Financial distress will be measured using the InCharge Financial Distress/Financial Well-Being scale, and HR-QOL will be measured by the cancer-specific FACT-G7 scale.

Each outcome will be evaluated in a separate model. We will use linear regression models to estimate group means, using generalized estimating equations (GEE) with an independent working correlation structure and robust covariance estimation. The dependent variable will be the 12-month study outcome (financial distress, or HR-QOL), and the independent variables will be indicator variables for randomization group. Models will account for the clustering of patients within oncology departments. Estimates of intervention effects will be presented as differences in group means, with 95% confidence intervals. We will fit unadjusted models, and models adjusting for covariates, and models adjusting for measures imbalanced by randomization group, related to missing outcome data, and baseline measures of the outcome (where appropriate).

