### Trial design {8}

The CAFÉ study is a multi-site randomized controlled trial (RCT) with individual-level randomization (Fig. 1). The study has three arms: enhanced usual care (Arm 1); brief intervention (Arm 2); and extended intervention (Arm 3).

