**Fig. 1 Fig1:**
[figure not shown]
CAFÉ study design overview

The intervention to be studied is a financial navigation intervention. Participants will be offered either brief (one financial navigation cycle, Arm 2) or extended (three financial navigation cycles, Arm 3) financial navigation. The intervention period for both Arms 2 and 3 is 6 months.

The comparison group (Arm 1) will receive enhanced usual care, defined as usual care plus a mailed financial resource sheet describing local and national organizations that serve people with cancer and may address financial concerns.

The original planned study was a clinic-level RCT with stepped wedge design. However, this design could be compromised in the case of COVID-19 related clinic closures, and other COVID-19 related time-trends affecting clinical care. Switching from the clinic-level stepped wedge design to an individual-randomized 3-arm trial protects against these threats to study validity. In addition, we adapted the CAFÉ intervention to be delivered remotely (phone), rather than at in-person visits, further protecting against COVID-19-related changes to clinical care. We chose a 3-group design to assess the impact of the study intervention at two different offered doses (Arms 2 and 3).

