## Methods: participants, interventions, and outcomes

### Study setting {9}

The setting for the CAFÉ study is the medical oncology and radiation oncology clinics at two integrated health systems: Kaiser Permanente Washington (KPWA) in Seattle, WA, and Kaiser Permanente Northwest (KPNW) in Portland, OR. We partnered with oncology leadership and business services in both regions to implement the study.

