## Assignment of interventions: allocation

### Sequence generation {16a}

After completion of baseline questionnaire, participants will be randomized via a computer-generated randomization scheme developed by a study biostatistician in a 1:1:1 ratio to study groups (Enhanced usual care, Brief intervention, or Extended intervention) stratified by site (KPWA; KPNW), and cancer type (breast, lung, prostate, colorectal, other). Our recruitment goal is to enroll a sample that reflects the distribution of cancer types in the underlying clinical population, and to enroll an equal number of participants at each study site. As such, we will flex the sampling during the recruitment period to meet this goal.

We will employ random blocks of sizes 3 and 6 to ensure balance of groups over time as well as blinding of study team to next randomization assignment. The biostatistician will keep the randomization file in a secure folder only accessible to the biostatisticians and programmer.

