#### Analysis of the secondary endpoint(s)

Analysis of secondary outcomes that are continuous such as out-of-pocket expenditure will follow the same analytic approach outlined for the primary outcomes. For binary outcomes, such as initiation of treatment, use of financial services (yes/no), or account delinquency, we will use modified Poisson regression models. Models will use a log link function estimated with GEE, with an independent working correlation structure and robust covariance estimation, and will account for clustering by oncology department. Intervention effects will be presented as the relative risk of the outcome in each of the intervention groups relative to Usual Care, with 95% confidence intervals.

To assess the short-term impact of financial navigation on health service use and treatment outcomes, we will conduct analysis of several secondary outcomes at 3 months. These include (1) medical financial assistance (MFA) application (yes/no) [Secondary: MFA application approved or denied; type of MFA award received] and (2) initiation of treatment (yes/no) [Secondary: time-to-initiation of treatment; type of treatment]. Assessment of 3-month outcomes will follow the general approach outlined for 12-month primary and secondary outcomes, except that the intervention group will be a binary variable. Group 2 (Brief intervention) and Group 3 (Extended intervention) participants will be combined for analysis, and effect estimates will compare this combined intervention group to usual care.

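### The robust variance is clustered on oncology department in an individually randomised trial that does not need it; if departments are few, either the 5% error rate or the 80% power is lost

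*Protocol article*

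**What the plan says.** Under Analysis of the primary endpoint(s), the protocol article estimates group means for both primary outcomes by linear regression, "using generalized estimating equations (GEE) with an independent working correlation structure and robust covariance estimation". It adds: "Models will account for the clustering of patients within oncology departments". Under Analysis of the secondary endpoint(s), continuous outcomes follow the same approach. Binary outcomes use modified Poisson GEE models that "will account for clustering by oncology department".

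Trial design {8} describes a "multi-site randomized controlled trial (RCT) with individual-level randomization". Sequence generation {16a} has allocation "stratified by site (KPWA; KPNW), and cancer type (breast, lung, prostate, colorectal, other"; department is not a stratum. Trial design also records that "The original planned study was a clinic-level RCT with stepped wedge design", which was replaced by individual randomisation.

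Study setting {9} gives the setting as the "medical oncology and radiation oncology clinics at two integrated health systems". No section says how many departments this makes. Sample size {14} promises 80% power at two-sided 0.05 for d = 0.40 with 99 analysed per group.

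**The concern.** With an independence working correlation, clustering can enter only through the sandwich variance. The department is therefore the unit from which every standard error is built, for both primary outcomes and for the secondary outcomes modelled the same way. A sandwich variance relies on many clusters. With few, it is biased low and unstable, and normal critical values make matters worse.

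The design gives no offsetting need for it. Patients in one department are allocated to all three arms, so a shared department effect largely cancels from the difference between arms. Clinic clustering would have been needed for the stepped wedge design, where the clinic was randomised; it is not needed for the present one.

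At stake are the coverage of the 95% confidence intervals and the error rate of the tests or, if a correction is applied, the power that justified 370 participants.

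**Working it through.** **Inputs from the protocol article.** 370 enrolled, 20% attrition, 296 analysed, 99 per group, two-sided alpha 0.05, 80% power, d = 0.40, SD 2.4 (InCharge) and 5.0 (FACT-G7), all from Sample size {14}. **Assumed, because not stated:** number of departments G from 4 to 40; intraclass correlation (ICC) 0 or 0.05; equal or unequal department sizes.

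**Step 1: reproduce the stated power.** 370 × 0.8 = 296, and 296/3 ≈ 99. The noncentrality is 0.40/√(2/99) = 2.81, and Φ(2.81 − 1.96) = 0.80. The stated 80% reproduces (0.804 when computed exactly). The minimum detectable d is 0.398, that is 0.956 on InCharge (stated 0.96) and 1.99 on FACT-G7 (stated 2.0). The formula treats patients as independent, with no design effect and no cluster degrees of freedom.

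**Step 2: type I error of an uncorrected department sandwich with critical value 1.96.** For equal department sizes this is approximately 2·P(t[G−1] > 1.96·√((G−1)/G)). With G = 4: 1.96 × √0.75 = 1.697, and 2·P(t[3] > 1.697) = 0.188. This was checked by null simulation: 5,000 trials per setting, 296 patients randomised individually 1:1:1, and the linear independence-GEE model.

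**Step 3: power at d = 0.40 with a G/(G−1) correction and a t(G−1) reference.** This is approximately P(|T| > t[0.975, G−1]), where T is noncentral t with G−1 degrees of freedom and noncentrality 2.81. With G = 4 the critical value is 3.182 and the power is 0.486.

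| Departments (G) | Type I error, uncorrected: closed form | Type I error, uncorrected: simulated | Power, corrected with t(G−1) |
|---|---|---|---|
| 4 | 18.8% | 19–20% | 49% |
| 6 | 13.4% | 13–15% | 62% |
| 8 | 10.9% | 11–12% | 68% |
| 10 | 9.6% | 10–12.5% | 71% |
| 20 | 7.1% | 7.5–10% | 76% |
| 40 | 6.0% | 6–9% | 78% |

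The upper ends of the simulated ranges come from unequal department sizes. Changing the ICC from 0 to 0.05 hardly moves the figures. With 4 departments, the estimated standard error averages about 77 to 80% of the true one. The chance of at least one false positive across the two arm-versus-control contrasts of a single outcome is then 32 to 35%.

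**Step 4: the alternatives under the same simulation.** A patient-level (model-based) variance gave 4.7 to 5.9% at every G and both ICC values, so the 80% of Step 1 stands. The corrected department variance with t(G−1) gave 4.4 to 5.4% with equal sizes and up to about 8% with very unequal sizes.

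**Step 5: two further checks.** A separate simulation (2,000 trials per setting, randomisation blocked within site and cancer type, ICC 0.02) gave 18 to 22% with 4 departments and 8 to 10% with 20 for the uncorrected department sandwich. Participant-level HC2 errors gave 4 to 6% throughout. A log-link binary analogue (370 patients, combined intervention arms versus control, event rate 0.20 assumed, uncorrected) gave 19%, 13%, 9%, 7% and 6% with 4, 6, 10, 20 and 40 departments.

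**The case against.** The strongest reply is that the inflation depends on two things the article does not fix. It gives no number of departments, and it names neither an uncorrected sandwich nor a normal reference distribution. A small-sample correction is the kind of detail that an SAP may carry, and the SAP is not shown. This stands. A reader might infer that there are certainly very few departments and that the intervals will be far too narrow, but the documents do not support that. Study setting {9} refers to clinics in the plural, and the eligibility criteria treat clinic and department as interchangeable. With 20 to 40 departments the excess error is modest.

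The reply does not rescue the choice, however. A correction moves the cost from error rate to power, and Sample size {14} allows for no such loss.

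Three other inferences should not be drawn:

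- **No unique cluster for patients seen in both specialties.** Eligibility rests on a qualifying clinic visit (Eligibility criteria {10}, Recruitment {15}), which supplies an index department.
- **Failure of the planned analysis because the cluster covariance matrix is rank-deficient.** The planned results are single differences in means and relative risks; no multi-parameter test is specified.
- **The clustering term as a leftover from the stepped wedge design.** "Switching from the clinic-level stepped wedge design to an individual-randomized 3-arm trial protects against these threats to study validity" explains the change of design but says nothing about the origin of the term.

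One point on the other side keeps some force. Care teams are told who is in Arms 2 and 3 and may initiate navigation, so the effect could vary by department. A participant-level variance would not fully reflect that. With modest variation of this kind its type I error was about 6%.

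**Conclusion.** The concern holds in conditional form. Clustering the robust variance on department is not wrong in itself: it would serve with many departments or with a proper correction. In this design it adds little validity and carries a cost that depends on a number the article never gives. If departments are few, an uncorrected analysis has a type I error of about 19% with 4, 13 to 15% with 6, 10 to 12.5% with 10 and 7 to 10% with 20. A corrected one has power of about 49%, 62%, 71% and 76% respectively, against the stated 80%. So with few departments, the analysis as described cannot deliver both the 0.05 error rate and the 80% power of Sample size {14}; a participant-level variance can.

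The figures assume normal outcomes, 296 analysed, an ICC of 0 to 0.05 and no clustering by navigator. The main simulation used simple rather than stratified block randomisation; the separate one with blocked randomisation agrees.

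**What to change.** 1. State the number of oncology departments and how each participant is assigned to one, for example by the qualifying visit.
2. Make participant-level robust standard errors (HC2 or HC3) primary for the linear and modified Poisson models, with the randomisation strata (site and cancer type) as fixed effects.
3. Report department clustering only as a sensitivity analysis, with a bias-corrected sandwich variance and small-sample (for example Satterthwaite) degrees of freedom.

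The cost is a change of wording in the two analysis sections, made before the 12-month data are unblinded. It needs no new data and no change to the sample size. The small downside is that department-by-arm variation, if present, is not reflected in the primary standard errors; the sensitivity analysis is there to show whether that matters.

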### Sample size {14}

The study will enroll 185 participants at each site (total *n*=370; approximately 123 per randomization group). Primary outcome measures for Objective 1, are assessed via survey at 12 months. Assuming 20% attrition, the analytic sample size for Aim 1 outcomes will be 296 patients (*n*=99 per group). With a type 1 error rate of 0.05 (two-sided), we will have 80% power to detect effect sizes of Cohen’s *d* = 0.40 for continuous outcomes. For the primary outcome of financial distress, this translates to a least detectable difference of 0.96 on the InCharge financial distress scale (10-point measure) for pairwise comparisons between randomization groups, assuming a standard deviation of 2.4 [41]. For the binary financial hardship measures (secondary outcomes), the least detectable difference depends on the proportion reporting financial hardship in the comparison group. We have 80% power to detect at 17.4% difference in financial hardship if the reported rate is 35% in the comparison group, corresponding to a rate of 17.6% among intervention patients (pairwise comparison of randomization groups). If the rate among comparison patients is much lower at 15%, the least detectable difference is 11.4%.

Based on our estimated sample size and a standard deviation of 5.0 as reported in the measure development work establishing the validity and reliability of the FACT-G7 in ambulatory cancer patient population [42], we estimate that we will be able to detect a 2.0-point difference in health-related quality of life (HR-QOL) between intervention and control groups. Since a 2 to 3 point difference on the FACT-G7 is considered clinically meaningful [42], we will be able to detect clinically meaningful changes on the FACT-G7 during the CAFÉ study.

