#### Survey

Participant-reported outcomes and covariate data will be collected via telephone survey at baseline and 12 months. Trained survey administrators will conduct all surveys using IRB-approved survey instruments. Survey administrators will enter survey data directly into the study REDCap database.

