### Methods in analysis to handle protocol non-adherence and any statistical methods to handle missing data {20c}

The investigators and data managers will monitor data collection process on a weekly basis and ensure a minimal amount of loss to follow-up in the study. All analyses will be conducted following a modified intent-to-treat approach, including all individuals randomized regardless of their engagement with, or exposure to the intervention. Individuals with missing outcome data will not be included in the primary analysis. We will conduct an analysis assessing factors related to missing outcome assessment. We will fit logistic regression models with missing primary outcome (yes/no) as the binary outcome in the logistic regression model, and baseline characteristic variables as independent variables, to determine predictors for missingness. Baseline covariates that are significantly (at 0.10 significance level) associated with missingness from this model will be adjusted in all models to ensure the validity of a missing-at-random (MAR) assumption. If loss to follow-up is above 15%, we will employ appropriate statistical techniques to address missing data issues. We will consider multiple-imputation analyses, or inverse probability weighting to account for missingness.

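### Each primary outcome gets several unranked models, some with data-chosen covariates; one should be named primary in advance, with baseline score, site and cancer type

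*Protocol article*

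**What the plan says.** Analysis of the primary endpoint(s) sets out a linear model, fitted by GEE, of the 12-month score on indicators for randomisation group, and reports differences in group means with 95% confidence intervals. On adjustment it says: "We will fit unadjusted models, and models adjusting for covariates, and models adjusting for measures imbalanced by randomization group". The same sentence then adds measures related to missing outcome data, and the baseline value of the outcome with the qualifier that this applies where suitable. No model is called primary.

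Four other places bear on this:

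- Sequence generation {16a}: randomisation is "stratified by site (KPWA; KPNW), and cancer type (breast, lung, prostate, colorectal, other". The primary-analysis text does not name these factors.
- Survey, under {18a}: "Participant-reported outcomes and covariate data will be collected via telephone survey at baseline and 12 months". Baseline scores on both primary scales should therefore be available.
- Missing data {20c}: "Baseline covariates that are significantly (at 0.10 significance level) associated with missingness from this model will be adjusted in all models".
- Sample size {14}: "Assuming 20% attrition, the analytic sample size for Aim 1 outcomes will be 296 patients", about 99 per group, with "80% power to detect effect sizes of Cohen’s *d* = 0.40 for continuous outcomes".

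**The concern.** A confirmatory analysis needs one result per primary outcome that was identified before the data were seen. Here at least three kinds of model are planned and none ranks above the others. If they disagree near the significance boundary, nothing in the text says which one answers the primary hypothesis.

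Two of the adjustment rules depend on the observed data. One brings in whatever looks imbalanced between arms, with no stated criterion. The other brings in whatever predicts missingness at the 0.10 level. Meanwhile the covariates with the best prior claim to a place in the model are either conditional (the baseline score) or unnamed (the strata).

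The missing-data section also adjusts every model for missingness predictors. If any covariate passes that screen, a model cannot both carry that adjustment and be unadjusted.

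**Working it through.** **1. The plan's own power figure.** Inputs from Sample size {14}: two-sided alpha 0.05, power 80%, d = 0.40, 370 enrolled, 20% attrition, SD 2.4 (InCharge) and 5.0 (FACT-G7).

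- Analysed: 370 × 0.8 = 296; 296 / 3 = 98.7, about 99 per arm.
- Detectable d = (1.960 + 0.842) × √(2/99) = 0.398. In scale points, 0.398 × 2.4 = 0.96 and 0.398 × 5.0 = 1.99.
- Power at d = 0.40 is 80.4% by the normal approximation and 80.0% by the noncentral t.

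The stated figures reproduce for an unadjusted pairwise comparison.

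**2. Effect of fixing the baseline score in the model.** The residual SD becomes SD × √(1 − r²), where r is the correlation between baseline and 12-month scores. The article gives no r, so a range is assumed. Power = Φ(0.40 / √(1 − r²) × √(99/2) − 1.960).

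| r (assumed) | Power at d = 0.40 | Detectable, InCharge | Detectable, FACT-G7 | Analysed per arm for 80% power |
|---|---|---|---|---|
| none | 80.4% | 0.96 | 1.99 | 99 |
| 0.3 | 83.9% | 0.91 | 1.90 | 90 |
| 0.5 | 90.1% | 0.83 | 1.72 | 74 |
| 0.7 | 97.6% | 0.68 | 1.42 | 51 |

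For r = 0.5: 0.40 / 0.866 × 7.036 − 1.960 = 1.29, and Φ(1.29) = 0.901.

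The further gain from site and cancer type cannot be computed, because their prognostic strength is not given. Their cost in degrees of freedom is small. Intercept, 2 arm terms, baseline score, 1 site term and 4 cancer-type terms make 9 parameters against 296 participants.

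**3. Does the imbalance rule damage the error rate?** Null simulation: three arms of 99, ordinary linear models, 10,000 runs, 8 candidate covariates (3 mildly prognostic, coefficient 0.2 each), imbalance screen at p < 0.10. The covariate numbers and the screening threshold are assumptions, since the article states neither. Results for one pairwise contrast at nominal 5%:

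| r | Unadjusted | Baseline plus imbalanced covariates | Smallest p of the three models |
|---|---|---|---|
| 0.3 | 5.3% | 5.2% | 8.4% |
| 0.5 | 5.2% | 4.4% | 9.0% |
| 0.7 | 5.0% | 4.4% | 9.4% |

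The Monte Carlo standard error at 5% is √(0.05 × 0.95 / 10,000) = 0.2 percentage points. A separate run of 20,000 replicates gave 4.8%, 4.1% and 3.5% for imbalance-screened adjustment as the covariates became more prognostic. So the screen alone is neutral to mildly conservative. Inflation, to about 8% to 9% here, appears only if the most favourable of the three models is reported as the result. The missingness screen was not simulated.

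**4. The two sections side by side.** Analysis of the primary endpoint(s) lists unadjusted models as a separate set and mentions missingness-related measures only within an adjusted set. Section {20c} applies missingness predictors to every model. Taken literally, the two are incompatible once any predictor passes the 0.10 screen.

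**The case against.** The strongest reply is that this is ordinary practice condensed for a journal. Under randomisation, unadjusted and adjusted linear models target the same mean difference, and reporting both is common. A full covariate list belongs in the full protocol or analysis plan. Covariate adjustment as described does not exclude site or cancer type, and leaving prognostic strata out of a linear model normally makes inference conservative rather than invalid. The qualifier on baseline adjustment may exist only because the same approach is reused for secondary outcomes with no natural baseline value, such as treatment initiation. Section {20c} may mean all adjusted models.

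Much of this stands, and it rules out several stronger readings that a reader might infer:

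- **That the imbalance rule invalidates the 5% error rate.** It does not. The screen uses only baseline data and arm, and the simulation shows no inflation from it.
- **That the primary result will be picked for significance.** The article says the models will be fitted. It nowhere says the best will be chosen.
- **That no treatment contrast is estimated.** Arm indicators give differences in group means, Sample size {14} refers to a "least detectable difference of 0.96 on the InCharge financial distress scale (10-point measure) for pairwise comparisons between randomization groups", and the secondary analysis compares each intervention group with usual care.
- **That the trial is underpowered.** The sample size holds without any adjustment.

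The reply does not reach what the article itself states: a list of models with no ranking, a data-driven covariate rule with no criterion, and two sections that disagree on whether an unadjusted model exists. An analysis plan that fixed one model would have to override this text.

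**Conclusion.** The point holds as a free improvement, not as a flaw that threatens validity. The primary model is not designated, part of the adjustment depends on the observed data, the strata are unnamed and the baseline score is conditional. The text on unadjusted models conflicts with the missing-data section.

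The cost is twofold. First, there is room for selective emphasis: about 8% to 9% type I error per contrast if the most favourable of three models were reported, under the illustrative assumptions above. The plan does not say this will happen. Second, precision is forgone if a model without the baseline score is taken as primary: roughly 4, 10 or 17 percentage points of power at r = 0.3, 0.5 or 0.7. That size rests wholly on the assumed r and, like the plan's own calculation, treats participants as independent.

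**What to change.** - Designate one primary model per outcome: 12-month score on arm indicators, baseline score of the same measure, site and cancer type, all fixed in advance. For the two primary scales, remove the qualifier on baseline adjustment.
- Delete the selection of covariates by observed imbalance between arms.
- Reconcile Analysis of the primary endpoint(s) with {20c} by stating which models take the missingness predictors, for example a named sensitivity analysis. The present wording applies them to every model.
- Label the unadjusted and further-adjusted models as sensitivity analyses.

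The cost is wording only. The baseline survey and both stratification factors are already collected, and sample size and conduct do not change. The change should be recorded before the 12-month data are unblinded.
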